### Aims and hypotheses

This study aims to evaluate the efficacy of the next iteration of our self-help internet cancer coping intervention (‘*Finding My Way’*) in improving wellbeing and quality of life of early-stage cancer patients over time, using a multi-site RCT.

A secondary aim is to investigate moderators of therapeutic change, consistent with recommendations that RCTs should identify who benefits most, and under what conditions, from psychosocial interventions [30]. For the present study, factors that have been previously shown to predict distress will be examined for their potential to moderate the effects of the intervention; namely, availability of social support, cognitive vulnerability to distress, and motivation to seek information [8,31].

Therefore it is hypothesised that:Intervention participants will report greater improvements compared to attention-control participants in the primary outcome, distress, from baseline to post-treatment and 3- and 6-month follow-up;Intervention participants will report greater improvements compared to attention-control participants in the secondary outcomes coping and HRQOL over time;Primary and secondary outcomes will be moderated such thatThe significant changes over time in distress between groups will be moderated by social support, cognitive vulnerability to distress, and motivation to seek information, andThe significant changes over time in coping and HRQOL between groups will be moderated by social support, cognitive vulnerability to distress, and motivation to seek information.

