#### Moderators of outcomes

Participant and medical characteristics, availability of social support, information-seeking preferences, emotion regulation, vulnerability to cancer-distress, adherence to the program, and participant satisfaction are assessed as postulated moderators of program efficacy.

Participant and medical characteristics are assessed at baseline only, and consist of age, marital status, occupational status, annual gross income, level of educational attainment, area of residence (rural/urban, state), ethnicity, cancer type, time since diagnosis, treatment received (surgery, chemotherapy, radiotherapy, hormonal therapy, other), any other chronic health conditions, and other support-services accessed.

Availability of social support is assessed using the 20-item Medical Outcome Study Social Support Survey [38], which consists of four subscales: emotional/informational, tangible, affectionate, and positive social interactions, with availability of the support type listed in each item rated on a 5-point scale (*1 = none of the time, 5 = all of the time*).

Information seeking preferences in terms of the type and amount of cancer information sought by patients is measured by the Miller Behavioral Style Scale scale [39]. This scale identifies information seekers who look for and amplify threat-related cues (monitors) and distracters who avoid and minimize such cues (blunters), and has been used extensively in cancer populations. The scale asks the respondent to imagine two stress-evoking scenarios, each of which is followed by eight statements that describe different ways of coping with the stressor, with four statements being of a monitoring or information-seeking variety and four of a blunting or information-avoiding variety. Respondents are asked to check all statements that apply to them.

Vulnerability to distress is assessed using the Difficulties in Emotion Regulation Scale [40], a 36-item measure of difficulties in emotion regulation across six dimensions, namely a) lack of awareness of emotional responses, b) lack of clarity of emotional responses, c) non-acceptance of emotional responses, d) limited access to emotion regulation strategies perceived as effective, e) difficulties controlling impulses when experiencing negative emotions, and f) difficulties engaging in goal-directed behaviours when experiencing negative emotions. Participants respond to each item on a 5-point scale (*1 = almost never, 5 = almost always*).

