### Analysis

#### Sample size

Longitudinal sample size calculation for repeated measures was conducted using a program developed by Hedeker [42]. Previous online interventions targeting distress in community samples have effect sizes ranging from .42 to .65 for depression, and from .29 to 1.74 for anxiety [19]. Therefore, a conservative small-to-moderate effect size was selected for the current study. Based on the pilot RCT findings, an attrition rate of 21% at each of the assessment points can be expected [29]. Thus for a study with 2 groups and 4 assessment points, power set at 0.80, statistical significance set at α = .05 (two tailed), total attrition set at 21%, an effect size set at 0.35 SD, and an expected primary endpoint standard deviation of 4.0 at each time point [43], 94 participants per group are required, summing to a total sample of 188 participants.

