#### Statistical analysis

Quantitative data will be analysed using the Statistical Package for the Social Sciences (SPSS) Version 17.0. Baseline differences between groups will be investigated using t-tests for continuous measures and *χ*^2^ tests of independence for categorical measures. Linear Mixed Effects Models (LMEM) will be employed to examine the efficacy of the intervention. The LMEM calculates a regression line for each individual while controlling for baseline observation (fixed main effects). Baseline observations will be entered as covariates to eliminate the influence of baseline variability, resulting in a 2 (group: intervention; control) X 3 (time: post-program; 3-month follow-up; 6 month follow-up) fixed effects model for each outcome variable, with random effects accounting for individual variation. This approach effectively equalises conditions at baseline and consequently allows for direct comparison between conditions at each follow-up point. In this context, (a) interactions between condition and time, (b) main effects of group and (c) post-hoc pairwise comparisons at each follow-up point are all indicators of intervention effects. This analysis offers the benefit of estimation maximisation; it provides joint modelling for each participant of observed and missing data based on maximising likelihood for population parameters as a function of the observed data. LMEM analyses are therefore robust with respect to handling missing data and unbalanced designs in longitudinal research as all participants with at least one observed *post-treatment* data point are included. That is, as baseline data is entered as a covariate, participants who do not complete any of the post-program assessments are not retained. To overcome this limitation and ensure this trial adopts a fully intention-to-treat design, multiple imputation will be performed for participants with only baseline-data. Therefore all participants, regardless of missing data at one or more assessment points, will be included in analyses and accurate parameter estimates obtained. Within-group effect sizes and reliable change indices will be calculated to provide a measure of the magnitude and clinical significance of changes respectively. To test for moderation, separate LMEM analyses will be conducted for each combination of moderator and outcome variable, where the moderator and group are entered in model 1 to control for main effects. The product term is then entered in model 2, to represent the interaction between group and moderating variable, and will indicate the moderating effect.

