
## Discussion

Internet-based self-help modalities represent one means of overcoming existing barriers to cancer patients accessing supportive care and psychosocial services, including the lack of such services within the public health system, particularly for rural patients, and barriers to attendance even where such services are provided. However, previous studies examining the efficacy of web-based self-help modalities for cancer populations have suffered from a range of limitations including (1) lack of an established psychological model (such as CBT) as the basis for the program, (2) lack of a control condition (3) small sample size and consequent lack of power for analyses, (4) lack of follow-up analysis over time, (5) examining efficacy of programs for one cancer type (i.e. breast cancer) only, as opposed to heterogeneous cancer types, and/or (6) examining programs implemented after completion of cancer treatment, as opposed to soon after diagnosis when distress tends to be highest and psychological treatment most warranted.

To our knowledge, *Finding My Way* is unique in offering an iCBT intervention applicable to individuals with heterogeneous cancer types soon after diagnosis. The large scale of this national multi-site RCT will therefore enable examination of the efficacy of such a program in reducing patient distress, improving coping and health related quality of life, and reducing health service utilisation in individuals with a range of cancer diagnoses. Furthermore, this study offers the important contribution of evaluating potential moderators of change. This information can be of benefit clinically when determining who to refer for online-interventions (versus who may be more suitably treated via other modalities) as well as benefitting future research via the refinement of inclusion and exclusion criteria, improving trial stratification and increasing power [30]. Indeed, it has been suggested that results of treatment trials are often weak because moderators of treatment are not examined, thus they should be part and parcel of any treatment study [30]; however, few studies have specifically examined moderators of psycho-oncology interventions.

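### Moderation is to be tested for every moderator-outcome pair, from a moderator list that differs between sections, so the three hypothesised tests are not set apart and chance findings are likely

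*Protocol article*

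**What the plan says.** Four parts of the protocol article bear on which moderators are tested, and a fifth on how the results may be used.

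- **Abstract, Methods/Design.** Potential moderators are described as baseline measures. Adherence and user satisfaction appear there as secondary outcomes.
- **Aims and hypotheses.** Moderation is a secondary aim and the third hypothesis. It names three factors, "availability of social support, cognitive vulnerability to distress, and motivation to seek information". The first part of the hypothesis concerns distress, the second coping and health-related quality of life (HRQOL).
- **Moderators of outcomes.** Seven classes "are assessed as postulated moderators of program efficacy": participant and medical characteristics, social support, information-seeking preferences, emotion regulation, vulnerability to cancer distress, adherence and satisfaction.
- **Statistical analysis.** "separate LMEM analyses will be conducted for each combination of moderator and outcome variable". Moderator and group enter in a first model and their product in a second; the product term is read as the moderating effect. The section does not limit the rule to the three hypothesised factors, rank the combinations or give a threshold.
- **Discussion.** "This information can be of benefit clinically when determining who to refer for online-interventions". The same paragraph mentions refining eligibility criteria and stratification in later research.

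**The concern.** The analysis rule is a positive instruction: run every pair and read each product term as evidence. Applied to the three hypothesised factors, it already produces several dozen tests. Applied to the list in the Moderators section, it produces a few hundred. A reader of the results could not tell from the plan which significant interactions answer the third hypothesis and which came from a wide search.

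Adherence and satisfaction raise a further difficulty. Both arise after allocation and the arm may affect them. The control version has no worksheets, for example, so the number of worksheets completed has no counterpart in that arm. An interaction with such a variable does not say who, at the time of referral, would benefit.

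What is at stake is the moderator conclusion, which the Discussion offers as useful for deciding whom to refer. The comparison of the two arms on distress does not depend on it.

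**Working it through.** **The plan's own figure.** The article gives no error rate and no number of tests for moderation, so there is no figure to reproduce. Its 94 per group concerns the main comparison and does not enter below.

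**Inputs from the article**

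- Outcomes: 2 distress measures (Primary outcome), 6 HRQOL scores (1 global + 5 functional) and 5 coping factors (Secondary outcomes). 2 + 6 + 5 = 13. Health service use is left out.
- Hypothesised moderators: 3 (Aims and hypotheses).
- Wider list: 7 classes (Moderators of outcomes). Counted singly, there are 12 participant and medical characteristics, plus social support, information seeking, emotion regulation/vulnerability (one scale), adherence and satisfaction. 12 + 5 = 17. Subscales of the moderator instruments are not counted.
- Alpha: .05 two-sided, stated only in the Sample size section. Its use for the moderation tests is an assumption.

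**Formulas**, with K tests and no true moderation

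- Expected false positives = K × 0.05. This holds whatever the correlation between tests.
- Chance of at least one, if independent = 1 − 0.95^K.
- Chance of at least one with correlation: simulated normal test statistics, with assumed correlations of 0.2-0.3 between moderators and 0.3-0.7 between outcomes.

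| Reading | K | Expected | At least one, independent | At least one, correlated |
|---|---|---|---|---|
| 3 moderators × 2 distress measures | 6 | 0.3 | 1 − 0.95^6 = 26% | 22-25% |
| 3 moderators × 13 outcomes | 39 | 1.95 | 1 − 0.95^39 = 86% | 55-80% |
| 7 classes × 13 outcomes | 91 | 4.6 | 1 − 0.95^91 = 99% | 82-97% |
| 17 variables × 13 outcomes | 221 | 11 | 1 − 0.95^221 > 99.9% | 98-100% |

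**The moderator lists side by side**

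- The Abstract's restriction to baseline measures excludes adherence and satisfaction; the Moderators section includes both.
- The Aims name three factors; the Moderators section names seven classes.
- The Statistical analysis section refers only to moderators, so it does not settle which list applies. Depending on the list, the same sentence commits the trial to 39 tests or to as many as 221.

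**The case against.** The strongest reply is that error control for a secondary aim is commonly left to a statistical analysis plan, which is not shown, and that an article condenses its protocol. That stands: the lack of a named correction is not the finding. It does not answer the all-combinations rule or the conflicting lists, which the article itself states.

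Several stronger readings are tempting, and the documents do not support them.

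- **That the article sets .05 for these tests.** It gives that level only for the sample size. All error rates here rest on carrying it over.
- **That chance findings are near certain for the hypothesised moderators.** The 86% needs 39 independent tests, and many outcomes are subscales of shared instruments. For that set the accurate word is likely. Only the wider lists come close to certainty, and the count of 17 depends on splitting one class into its 12 items.
- **That nothing limits the search.** The Aims do limit the hypothesis to three factors. Its reference to significant changes between groups could even mean testing moderation only where a group effect is found. But the Statistical analysis section carries neither limit over.
- **That most positive moderators would be false because interactions are underpowered.** This needs an effect definition and a share of true moderators, and the article gives neither. The hypothesised moderators are measured by scales with no stated dichotomising, so a power figure for an evenly split binary moderator does not describe this design.
- **That the results would decide referral.** The Discussion says only that they can be of benefit; it sets no decision rule.

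**Conclusion.** The point holds in a limited form. The article commits to testing every moderator-outcome pair while its sections disagree on the moderator set, and the analysis rule does not separate the three hypothesised factors from the rest.

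With no true moderation and .05 per test, about 2 false positives are expected on the narrow reading and about 11 on the broadest. Those counts need no independence assumption. The chance of at least one is 55-86% for the hypothesised set across the correlations considered, and at least 98% for the broadest list. The correlations and the count of 17 are assumptions.

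This affects what can be concluded about moderators and any use of that for referral.

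**What to change.** 1. Reconcile the Abstract, Aims and hypotheses, Moderators of outcomes and Statistical analysis sections, so that confirmatory moderation covers only the three hypothesised baseline moderators.
2. Make the two distress measures the confirmatory family: 3 × 2 = 6 tests under Holm, with the smallest p-value compared with 0.05/6 = 0.0083.
3. Test the coping and HRQOL part of the third hypothesis (3 × 11 = 33 tests) as a separate, lower-ranked family, or label it exploratory.
4. Label all other combinations exploratory, including those with adherence and satisfaction. Report their interaction estimates with confidence intervals and draw no referral conclusion from them.

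**Cost.** No change to data collection or sample size. Fewer moderators can be declared, and the coping and HRQOL moderation hypothesis ranks lower than it does now. This changes the standing of a stated hypothesis, so the Aims must be edited as well as the analysis text. Holm on six tests is one defensible choice among several. The essential step is to fix a small confirmatory set in advance and control error within it.

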
## Discussion

Internet-based self-help modalities represent one means of overcoming existing barriers to cancer patients accessing supportive care and psychosocial services, including the lack of such services within the public health system, particularly for rural patients, and barriers to attendance even where such services are provided. However, previous studies examining the efficacy of web-based self-help modalities for cancer populations have suffered from a range of limitations including (1) lack of an established psychological model (such as CBT) as the basis for the program, (2) lack of a control condition (3) small sample size and consequent lack of power for analyses, (4) lack of follow-up analysis over time, (5) examining efficacy of programs for one cancer type (i.e. breast cancer) only, as opposed to heterogeneous cancer types, and/or (6) examining programs implemented after completion of cancer treatment, as opposed to soon after diagnosis when distress tends to be highest and psychological treatment most warranted.

To our knowledge, *Finding My Way* is unique in offering an iCBT intervention applicable to individuals with heterogeneous cancer types soon after diagnosis. The large scale of this national multi-site RCT will therefore enable examination of the efficacy of such a program in reducing patient distress, improving coping and health related quality of life, and reducing health service utilisation in individuals with a range of cancer diagnoses. Furthermore, this study offers the important contribution of evaluating potential moderators of change. This information can be of benefit clinically when determining who to refer for online-interventions (versus who may be more suitably treated via other modalities) as well as benefitting future research via the refinement of inclusion and exclusion criteria, improving trial stratification and increasing power [30]. Indeed, it has been suggested that results of treatment trials are often weak because moderators of treatment are not examined, thus they should be part and parcel of any treatment study [30]; however, few studies have specifically examined moderators of psycho-oncology interventions.

If found efficacious, *Finding My Way* will represent an important means of overcoming common barriers to face-to-face therapy in a cost-effective and accessible way, which may particularly assist those residing in rural/remote areas. Integration of such a program into the supportive care offered to cancer patients within the health system will therefore be a promising avenue for reducing patient distress after cancer diagnosis, and consequently for decreasing the cancer burden both on individuals and within the health system.

## Abbreviations

CBT: Cognitive behaviour therapy
DASS: Depression anxiety stress scales
ES: Effect size
FMW: Finding My Way
HRQoL: Health related quality of life
iCBT: Internet cognitive behaviour therapy
ISG: Internet support group
LMEM: Linear mixed effects models
mini-MAC: Mini Mental Adjustment to Cancer Scale
QOL: Quality of life
RCT: Randomised controlled trial
SET: Supportive expressive therapy
SPSS: Statistical package for the social sciences
